#### Functional outcome measures and frailty

Functional capacity will be measured objectively by the six-minute walk test (6MWT), conducted according to American Thoracic Society guidelines [37]. This simple, practical and inexpensive sub-maximal exercise test assesses functional capacity [38], is closely linked to activities of daily living and has been proposed as both a functional status indicator and an outcome measure [39]. Similarly, gait speed is an important indicator of frailty [40], with slow gait a strong predictor of adverse outcomes, including disability, high healthcare utilisation and mortality [41].

Frailty describes a vulnerability to adverse events that is associated with, but separate from chronological age [42]. Implicitly, all patients requiring TAVI as opposed to open aortic valve surgery must have frailty as a barrier to standard treatment. Frailty is therefore an important contributor to the choice of TAVI and a potential confounder regarding outcomes, including delirium [43]. The SANITY study will utilise the Deficit accumulation score, which provides a robust measure of frailty and an appreciation of those who are unable to complete performance based tests - the frailest frail [44].

### Endpoint definitions

The endpoints for the SANITY study are outlined in Figure 4. The primary endpoint focuses on the characterisation and quantification of the neurological injury as detected by new ischemic lesions on MRI. Secondary endpoints focus on the clinically apparent neurological injury sustained and markers of insult/injury.

**Figure 4 F4:**
[figure not shown]
Overview of SANITY variables and endpoints.

### Statistical analysis

An estimated 100 patients will be recruited into this study, fifty in each of the two treatment arms (SAVR and TAVI) and at least 20 patients in each TAVI subgroup (transfemoral and transapical/transaortic). Fifty patients per group provides 90% power to detect differences in the incidence of new DWI lesions (primary endpoint) with two-sided statistical significance of 5%, assuming overall incidence estimates of 76% and 45% with TAVI and SAVR, respectively, as previously reported.

Multiple regression models will be used to adjust for potential confounders identified based upon clinical importance and statistical selection. The key output will be the estimated treatment difference and 95% confidence intervals for the primary group from the multiple regression models. Additionally, longitudinal analysis will be used to examine all outcomes with repeated data, again using multiple regression models. Treatment failure and withdrawal will be considered on an intention-to-treat basis, with the aim of providing a more realistic estimate of the difference between groups in clinical practice.

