## Methods

### Study design

This is a prospective, multicentre, non-randomised and observational study comparing the incidence of neurological injury associated with TAVI of the Edwards SAPIEN-XT (Edwards LifeSciences Irvine, CA, USA) under general anaesthetic versus bioprosthetic SAVR. Ethics approval has been obtained from the Human Research Ethics Committee of the Prince Charles Hospital, Brisbane, Australia (HREC/12/QPCH/291) and informed consent will be obtained from all participants prior to enrolment.

Regularly held 'Heart Team’ meetings - comprising of multiple disciplines including echocardiologists, interventional cardiologists, nurses and cardiothoracic surgeons – will assess high-risk patients with severe AS. Here, patients will be allocated to the intervention clinically indicated. Pending informed consent, such patients will be consecutively recruited into the SANITY study, resulting in cohort grouping as outlined in Figure 2.

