### Patient population

Thorough pre-, intra- and post-procedural assessments allow results to be adjusted for baseline status, thus permitting an inclusive approach to enrolment. As such, only patients unable to participate in aspects of assessment or enrolled in other studies (Table 2) will be excluded.

**Table 2 T2:** Eligibility criteria

**Inclusion criteria**	**Exclusion criteria**
I. Informed consent for participation	I. Lacks capacity to consent for him or herself
II. Severe aortic stenosis	
i. AVA <0.8 cm^2^	II. Pre-existing neurological impairment
ii. Mean aortic valve gradient >40 mmHg	i. Modified rankin score ≥ 3 (i.e. moderate disability; requiring some help, but able to walk without assistance)
iii. Peak jet velocity >4 m/s	
III. Planned TAVI or SAVR	
IV. High-surgical-risk	III. Contraindication to MRI (including incompatible metallic prosthesis/foreign body, inability to lie flat, claustrophobia requiring sedation)
i. STS score >8%	
ii. Logistic EuroSCORE >20%	
iii. Logistic EuroSCORE II >10%	IV. Non or poor English-speaking due to nature of and unknown validity in such populations cognitive testing
	V. Previous aortic valve repair/replacement
	VI. Coronary artery disease requiring revascularisation (including patients undergoing combined AVR and CABG)

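### Choosing confounders for the primary TAVI versus SAVR model partly by statistical selection can drop measured confounders and give a 95% confidence interval that is too narrow

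*Protocol article*

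**What the plan says.** The Statistical analysis section of the protocol article sets the rule for adjustment: "Multiple regression models will be used to adjust for potential confounders identified based upon clinical importance and statistical selection". The next sentence gives the result of that rule its weight: "The key output will be the estimated treatment difference and 95% confidence intervals for the primary group from the multiple regression models".

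The Study design section describes a non-randomised comparison in which a Heart Team decides the procedure: "Here, patients will be allocated to the intervention clinically indicated". The section on functional outcome measures and frailty names frailty as a driver of the choice of TAVI and a possible confounder. The Limitations section says that level of health risk helps decide who is suitable for surgery, and gives multiple regression as the means of reducing confounding. It concedes bias from unmeasured confounders. It does not mention losing measured ones through selection.

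The planned size is 50 patients per group, with 90% power at a two-sided 5% level, "assuming overall incidence estimates of 76% and 45% with TAVI and SAVR, respectively, as previously reported".

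**The concern.** Regression is the study's main protection against confounding by indication, so the choice of covariates largely decides whether the primary estimate can be believed. Selecting them on the same data raises two problems.

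- **Residual confounding.** With about 100 patients, a moderate confounder often misses a p-value threshold. Dropping it puts its share of the bias back into the procedure effect.
- **Over-precision.** The usual standard error treats the final model as if it had been fixed beforehand. It leaves out the variability added by the search.

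Both act on the figure that the study calls its key output. This is a method that the article states, not a detail it leaves to an analysis plan, and an analysis plan that follows the text would carry it forward.

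**Working it through.** **1. The plan's own power figure.** Inputs from Statistical analysis: n = 50 per group, 76% and 45%, two-sided 5%. The mean rate is (0.76 + 0.45)/2 = 0.605.

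z = [0.31·√50 − 1.96·√(2·0.605·0.395)] / √(0.76·0.24 + 0.45·0.55) = (2.192 − 1.355)/0.656 = 1.277, which gives power 89.9%.

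The stated 90% is reproduced (51 per group would be needed for exactly 90%). It applies to the unadjusted comparison.

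**2. Information available for adjustment.** Expected patients with new lesions: 50·0.76 + 50·0.45 = 60.5. Expected lesion-free: 39.5. At 10 per parameter this supports 39.5/10, about 4 parameters; at 5 per parameter, about 8.

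**3. Effect of selection.** There is no closed formula, so this was simulated with 50 patients per arm and no true procedure effect (θ = 0):

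logit P(lesion) = 0.4 + θ(T − 0.5) + β·ΣC_k

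Here T marks the arm, and C_1 to C_K are independent covariates with SD 1 whose arm means differ by δ. Backward elimination with an ordinary Wald 95% interval was compared with the same covariates all forced in. **K, δ, β and the stay-in p are assumptions; the documents give none of them.** Kδβ is the total confounding on the log-odds scale. For scale, the planned effect is ln(0.76/0.24) − ln(0.45/0.55) = 1.35. With 1000 runs and coverage near 90%, simulation error is about √(0.9·0.1/1000) = 1 percentage point.

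| K | δ | β | Kδβ | Forced in | Stay-in p | Coverage, selected | Coverage, all forced |
|---|---|---|---|---|---|---|---|
| 10 | 0.3 | 0.20 | 0.60 | 0 | 0.10 | 86–87% | 94–95% |
| 10 | 0.4 | 0.25 | 1.00 | 0 | 0.10 | 79–81% | 94% |
| 4 | 0.4 | 0.30 | 0.48 | 0 | 0.10 | 90–91% | 94–95% |
| 6 | 0.5 | 0.30 | 0.90 | 0 | 0.05 | 76% | 96% |
| 6 | 0.5 | 0.30 | 0.90 | 3 | 0.05 | 89% | 94% |
| 6 | 0.5 | 0.30 | 0.90 | 3 | 0.20 | 93% | 95% |
| 10 | 0.3 | 0.20 | 0.60 | 5 | not recorded | 91% | 94% |
| 6 | 0.1 | 0.10 | 0.06 | 0 | 0.05 | 94% | 94% |

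**4. Both mechanisms in one scenario.** In the fourth row, selection leaves a bias of +0.44 in the log odds ratio, a spurious odds ratio of e^0.44 = 1.55. The mean reported standard error is 0.46 against a true SD of 0.57, and 1 − 0.46/0.57 = 19%, so the interval is about 19% too narrow. The prespecified model has bias −0.02, standard error 0.55 and SD 0.56.

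**5. Sensitivity to the assumptions.** Ten confounders with δ of 0.3–0.5, β of 0.3–0.4 and p 0.05 took coverage to 58–79%, the unfavourable end. Other variations were milder:

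- Covariates correlated at 0.5: bias fell from 0.28 to 0.06, with coverage about 91–93%.
- Confounders acting in mixed directions: bias 0, coverage 91% (93% all forced).
- Change-in-estimate selection: coverage 94.6% with no bias, where p-value elimination gave 88.6% (K = 6, δ = 0.4, β = 0.25). With 10 covariates, 92.7% against 86.3%.

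**6. Forcing in everything is not the answer either.** With the true log odds ratio at 1.35, ten forced covariates overstate it by 0.27–0.34 and six by 0.17–0.18. The prespecified set therefore has to be short, or shrunk.

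**The case against.** The strongest case is that selection is only half of the stated rule. Clinical importance comes first, and if it forces in frailty and a risk score, little is left for selection to damage. Nor does the article name a selection method, so p-value elimination is only one reading. This largely stands on size: forcing some covariates in brings coverage to about 87–94%, and a liberal threshold or change-in-estimate selection brings it close to a fixed model. It does not remove the point. The text does not say that clinically important variables are kept regardless. It equally allows a clinical shortlist that is then pruned statistically.

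A second objection is that a covariate list belongs in an analysis plan that is not shown. That is right, and the absence of a list is not the finding. The finding is the selection rule that the article does state.

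Two stronger readings are tempting, and the documents do not support them.

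- **Adjustment for mediators.** A reader might infer from the Patient population section that the primary model would adjust for events during or after the procedure: "Thorough pre-, intra- and post-procedural assessments allow results to be adjusted for baseline status". But that sentence gives baseline status as the target, and Statistical analysis limits adjustment to potential confounders. The Objectives place pacing, desaturation and new atrial fibrillation among the secondary associations.
- **A false-positive rate of 14–21%.** This corresponds to coverage of 86% and 79% in the first two rows of the table. It assumes ten independent confounders acting in one direction, all put through p-value elimination with none kept on clinical grounds. It does not describe the stated plan.

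**Conclusion.** The concern holds as a weakness in a stated rule. The primary estimate comes from a model chosen partly on the data, in a small non-randomised study, with an ordinary interval that takes no account of the choice. If selection is by p-value and confounding is material, coverage is about 79–92% with pure selection at p<0.10 (lower with a stricter threshold and stronger confounding). It is about 87–94% with some covariates forced in, against about 93–96% for a prespecified model.

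These figures rest on assumed confounder numbers and strengths; in the scenarios showing material loss, total confounding is roughly a third to three-quarters of the planned effect (0.48/1.35 = 36%; 1.00/1.35 = 74%). With weak confounding, a liberal threshold or change-in-estimate selection the loss is small. The estimate could be biased and over-precise; the text does not establish that it would be.

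**What to change.** For the primary TAVI versus SAVR model, replace selection by clinical importance and statistics with a short set of pre-procedure covariates, fixed in advance on clinical grounds and kept in whatever their p-values. Suitable candidates are age, EuroSCORE II or STS score, the Deficit accumulation frailty score and the echocardiographic calcification score. The article already plans both risk scores, the frailty score and baseline echocardiography in all patients.

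Size the set to about four parameters. Counting the procedure term, three covariates make four parameters (39.5/4 = 9.9 lesion-free patients each) and four make five (39.5/5 = 7.9). If more covariates are wanted, combine them in a propensity score or use a penalised model. Keep data-driven selection as a sensitivity analysis, with its rule stated. One added sentence confirming that only pre-procedure variables enter this model would close the mediator question.

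The cost is a change of wording before data are seen, and a somewhat wider interval: 0.55/0.46 = 1.20 times as wide in the scenario of step 4, and 0.551/0.506 = 1.09 times in the matching scenario with three of six forced in. Little real precision is lost. In step 4 the true SDs were 0.56 with the fixed model and 0.57 with selection.

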## Discussion

The SANITY Study offers the most comprehensive neurological/neurocognitive assessment of the TAVI and high-risk SAVR patient population to date. Additionally, well-established and recommended assessments are complemented by those that are novel and unique, thereby offering the potential of improved understanding of the interventions in question, correlation of risk factors and prognostic markers, and validation of assessment tools themselves. Such knowledge is vital to establishing both suitable assessment batteries and guidelines in this unique, high-risk group of patients, and to advancing strategies for neurological injury reduction.

### Limitations

Across all TAVI literature, the identification of risk-matched control groups has proven controversial. The validity of high-risk SAVR patients as a 'control group’ has previously been questioned, given that the level of health risk is a factor determining suitability for the procedure. Such difference also exists between access approaches, with transapical/transaortic typically considered a second line option where severe vascular disease excludes a transfemoral approach. Furthermore, these procedures differ vastly, most notably in the use of cardiopulmonary bypass, obscuring the exact cause of any difference identified between study groups. However, comparison between these two groups does offer clinical relevance as SAVR is the current 'gold-standard’ for eligible patients with AS and the challenge is in selecting the most appropriate procedure in patients who are considered suitable for both.

This study will be non-randomised and non-blinded. Though multiple regression analysis will be used to minimise confounding, this is not a substitute for blinding or randomisation, and unmeasured confounders may produce hidden bias.

Finally, a clinical follow-up duration of 6 months limits conclusions regarding delayed and late neurological injury. However, such a timeframe can be justified, given that DWI findings resolve within this period and reversible neurocognitive deficits generally resolve by 3 months [12]. Consequently, the financial costs and patient burdens of prolonging follow-up cannot be ethically justified.

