### Hypotheses

Based on the current concept of neurological insult and extrapolation of procedural risk factors for embolisation, it is hypothesised that neurological injury is less pronounced with:

1. SAVR than TAVI, due to the removal of the valvular source of embolisation, which in TAVI persists, pushed against the wall of the aorta and potentially acting as a nidus for calcific emboli and altered rheology, promoting thrombosis.

2. A transapical/transaortic than transfemoral approach. Transapical/transaortic routes minimise the risk of disrupting calcific plaques especially in the aortic arch, an inherent risk with femoral access.

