### Data collection

The complete assessment regime and timing of each component can be found in Figure 3. Where relevant, this regime was designed to be consistent with the assessments and endpoints recommended by the *Valve Academic Research Consortium* updated standardised endpoints (VARC-2) [17]. A multi-disciplinary approach has been adopted to ensure that relevant experts address each assessment domain.

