#### Magnetic resonance imaging *(*MRI*)*

Recognised as the most sensitive technique for the detection of acute ischemic cerebral infarcts, DWI detects the restriction of water diffusion in cerebral tissue caused by hypoxic oedema within minutes of ischemia onset. Increased signal intensity on DWI is reliably Detectable 4 hours post-insult and persists for up to 10 days [26]. Lesions representing brain infarct can be quantified in number, size, and volume using this modality.

Susceptibility Weighted Imaging (SWI) is a relatively new MRI sequence which is highly sensitive to the local magnetic field inhomogeneity caused by paramagnetic substances including the haem group in haemoglobin. SWI is commonly used as an adjunct to DWI in the assessment of cerebral ischemia as it is extremely sensitive for detecting haemorrhagic transformation within regions of infarction; can demonstrate acute thromboemboli sufficient to occlude arteries and can detect micro-haemorrhage, suspected to originate from diapedesis of red blood cells across overtly permeable capillaries. Peak incidence of haemorrhagic transformation occurs between 48 hours and 5 days and can persist for years [27].

Patients will undergo a baseline MRI study <48 hours prior to intervention. This comprehensive study will include standard fast spin echo sequences, baseline DWI and SWI sequences and time of flight angiography of the circle of Willis to document pre-existing disease. At day 4 (±2) post-intervention, and following removal of temporary pacing wires where applicable, a limited study consisting of DWI, SWI, T2 Flair and T1-weighted imaging will be performed. This interval length allows for sufficient patient recovery post-procedure to safely undergo an MRI examination and allows for establishment of the MRI detectable changes and maximum evolution of the ischemic change [28]. This limited acquisition is performed in 15 min for increased patient tolerance. A further limited examination after 6 months will include DWI and SWI, demonstrating DWI resolution, infarct complications and finally accounting for all SWI lesions.

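### The article calls the whole study non-blinded and makes no exception for reading the primary MRI endpoint, where masking the reader is feasible and cheap

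*Protocol article*

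**What the plan says.** The Limitations section of the Discussion says of the study as a whole: "This study will be non-randomised and non-blinded". It then says of multiple regression that "this is not a substitute for blinding or randomisation, and unmeasured confounders may produce hidden bias". It does not distinguish masking of patients and treating staff from masking of the person who reads the outcome.

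Under Endpoint definitions, "The primary endpoint focuses on the characterisation and quantification of the neurological injury as detected by new ischemic lesions on MRI". The MRI section adds that "Lesions representing brain infarct can be quantified in number, size, and volume using this modality". It sets a baseline study less than 48 hours before intervention and a further limited examination after 6 months. For the scan at day 4 (±2), "a limited study consisting of DWI, SWI, T2 Flair and T1-weighted imaging will be performed". None of this says who reads the scans or what that person knows. Data collection says only that "A multi-disciplinary approach has been adopted to ensure that relevant experts address each assessment domain".

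The Hypotheses section fixes a direction in advance: "it is hypothesised that neurological injury is less pronounced with" "SAVR than TAVI, due to the removal of the valvular source of embolisation". It gives a second directional hypothesis by access route, with less injury expected from transapical or transaortic than from transfemoral access.

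**The concern.** Whether a DWI focus is present, and whether it is new against baseline, is a reader's judgement. The sample size treats the endpoint as a yes/no incidence, so one equivocal focus can change a patient's classification. The hypothesis section and the quoted literature rates tell a reader who knows the procedure which answer is expected in which arm.

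If equivocal foci are resolved in that direction, the misclassification depends on the arm. It adds directly to the estimated treatment difference, which the Statistical analysis section calls the key output. Regression on patient characteristics does not remove it, because the error lies in the outcome and is tied to the treatment itself. The same readings also feed the secondary associations with clinical injury, calcification, cerebral desaturation, S100B and GFAP.

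The lack of randomisation is built into the design, since the Heart Team allocates treatment. Knowledge of treatment by patients and operators is equally built in. Unmasked reading of stored brain images is not, yet the one sentence covers all of these.

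**Working it through.** **Inputs from the Statistical analysis section.** 50 patients per arm; two-sided 5% level; 90% power; assumed incidences 76% (TAVI) and 45% (SAVR).

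**The plan's own figure.** For a two-proportion z-test with pooled null variance:

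- Difference d = 0.76 − 0.45 = 0.31; mean proportion 0.605.
- Null standard error = √(2 × 0.605 × 0.395 / 50) = 0.0978.
- Alternative standard error = √(0.76 × 0.24 / 50 + 0.45 × 0.55 / 50) = 0.0927.
- Power = Φ((0.31 − 1.96 × 0.0978) / 0.0927) = Φ(1.277) = 89.9%.

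The stated 90% reproduces, so the point does not rest on a numerical error. Masking the reader alters none of these inputs: 50 per arm and the power stay as they are.

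**What unmasked reading could do (illustration).** Assume that the true incidence p is the same in both arms. Assume also that the reader calls a new lesion in a fraction f of lesion-free TAVI scans and reads SAVR scans correctly. Then:

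- Observed TAVI incidence = p + f(1 − p); observed SAVR incidence = p.
- Spurious difference = f(1 − p).
- Type I error = Φ((d − 1.96·SE₀)/SE₁) + Φ((−d − 1.96·SE₀)/SE₁), with SE₀ pooled and SE₁ unpooled as above.

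The fraction f is not in the documents. The two values of p are the protocol's own planning incidences, used as the ends of a range.

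| Shared true incidence p | f | Observed TAVI vs SAVR | Spurious difference (points) | Type I error |
|---|---|---|---|---|
| 45% | 0 | 45.0% vs 45% | 0 | 5.0% |
| 45% | 5% | 47.75% vs 45% | 2.75 | 5.9% |
| 45% | 10% | 50.5% vs 45% | 5.5 | 8.5% |
| 45% | 20% | 56.0% vs 45% | 11.0 | 19.5% |
| 76% | 5% | 77.2% vs 76% | 1.2 | 5.2% |
| 76% | 10% | 78.4% vs 76% | 2.4 | 5.9% |
| 76% | 20% | 80.8% vs 76% | 4.8 | 8.9% |

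Worked line for p = 45%, f = 10%: d = 0.055, SE₀ = 0.0999, SE₁ = 0.0997. This gives Φ(−1.41) + Φ(−2.51) = 7.9% + 0.6% = 8.5%. With an unpooled test, the 20% rows become 19.8% and 9.0%.

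**A harsher assumption.** If the reader also misses a fraction f of true SAVR lesions, the spurious difference is f(1 − p) + fp = f at any incidence. Type I error is then about 8% to 9% at f = 5%, 17% to 20% at f = 10%, and 52% to 60% at f = 20%, over p from 45% to 76%.

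**Limits of the calculation.** It uses a crude two-proportion test in place of the planned regression model and sets confounding aside. It isolates the reader's contribution only.

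**The case against.** The strongest reply is that the sentence is being asked to carry too much. It stands in a Limitations paragraph about allocation and confounding, where non-blinded most naturally describes patients and treating staff. Nothing in the article says that the MRI reader will know the procedure. Reader masking usually belongs in an imaging charter or the full protocol, neither of which is shown, and the figures that summarise assessments and endpoints are not visible. Each patient also has a paired baseline scan, which limits the room for judgement about whether a lesion is new.

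Much of this stands:

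- A reader might infer that the article states the scans will be read unmasked. It does not; it describes no reader.
- A reader might infer that the article presents non-blinding as unavoidable. It discloses the limitation but does not say that.
- The over-calling rates have no support in the documents. At an incidence of 76%, one-directional over-calling has a much smaller effect than at 45%.
- It is tempting to ask for masking of the CT, echocardiographic and cerebral oximetry measures too. The documents do not support that extension. The aortic calcium score is described as quantitative, oximetry is an instrument reading with stated thresholds, no bias is shown for any of these measures, and none is the primary endpoint.

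What does not stand is that this is mere silence left to a longer document. The article makes a positive, unqualified statement about the study. If the full protocol masks the reader, that statement is too broad. If it does not, the primary endpoint is exposed to an avoidable bias. The sentence needs changing in either case.

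**Conclusion.** The point holds as a should-fix. As written, the non-blinded statement covers the reading of the primary endpoint, and no other section takes it back. Followed literally, it permits misclassification by arm in the direction already hypothesised.

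The size cannot be derived from the documents. With no true difference, 50 per arm and over-calling confined to 10% to 20% of lesion-free TAVI scans, the spurious difference is 5.5 to 11 percentage points at a shared incidence of 45%, and 2.4 to 4.8 points at 76%. The type I error is about 8.5% to 20% and about 6% to 9% respectively. Even the largest of these differences is well short of the planned 31 points, so reader bias at these rates would distort the estimate but would not by itself account for the whole planned effect.

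That masking is feasible is an inference from the nature of stored brain images. Masking reduces bias that comes from knowing the procedure; it would not remove every reader error, because lesion or SWI patterns may sometimes hint at the procedure. Confounding by indication, which the article already discloses, is untouched.

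**What to change.** Replace the sentence in Limitations with wording such as:

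*The study is non-randomised and open-label for patients and treating staff. The research reading of the baseline, day-4 and 6-month MRI is done on de-identified scans, in random order across arms, masked to procedure, access route, clinical neurological findings and biomarkers.*

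Each patient's scans should stay together as a set, because a lesion is new only against that patient's baseline. If the full protocol already masks the reader, it is enough to correct the article so that it says so.

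The cost is de-identifying and reordering the images before research reading, and keeping any clinical read for patient care separate from the research read. No additional scan is needed, and the sample size and power do not change. The arrangement should be in place before research reading begins.
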